# Protocol for a single-centre, parallel-arm, double-blind randomised trial evaluating the effects of tourniquet use in total knee arthroplasty on intra-operative and post-operative outcomes

**DOI:** 10.1186/s12891-018-2352-8

**Published:** 2018-12-06

**Keywords:** Knee arthroplasty, Tourniquet, Knee pain, Quadriceps strength

## Abstract

**Background:**

Tourniquet use during total knee replacement is common, yet uncertainty exists regarding its benefits and harms. The primary aim of the current study is to investigate whether tourniquet use during total knee replacement leads to greater reduction in quadriceps strength than non-tourniquet use at three months post-surgery. Secondary aims include investigating the effects of tourniquet use on: quadriceps strength at day 2 and 5, and 12 months post-surgery; pain and analgesia requirements; self-reported physical function and quality of life; blood loss and replacement; surgeon satisfaction with the intra-operative visual field; operation and anaesthetic time; complications; cement mantle quality; patient satisfaction; and hospital length of stay.

**Methods:**

The study is a single centre, parallel-arm, double-blind (participant and assessor), randomised trial with 1:1 random allocation. Participants will be undergo total knee replacement with or without tourniquet. Linear mixed models will be used for group comparisons of continuous outcomes available at multiple timepoints. Other continuous outcomes that are assessed at baseline and once/twice at follow-up will be analysed using linear regression. Categorical outcomes will be analysed using logistic regression models.

**Discussion:**

This study will provide high-quality evidence regarding the effects of tourniquet use during total knee replacement, which can be used to inform surgeon decision-making.

**Trial registration:**

Australian New Zealand Clinical Trials Registry ACTRN12618000425291. Retrospectively registered 23 March 2018.

## Background

Total knee replacement (TKR) is a common and successful procedure, with over 1 million TKRs occurring annually in OECD countries [1]. TKR is regularly performed using a tourniquet, with usage in 37–93% of surgeries [2, 3]. However, tourniquet use during TKR is debated due to evidence questioning the advantages, and the possibility of increased complications [4, 5].

A thigh tourniquet compresses the leg and restricts distal blood flow which is intended to reduce intra-operative blood loss at the surgical site. Tourniquet use has been suggested to improve surgical field view, allow cement to bond more effectively [6], and produce shorter operating time which might reduce the risk of infection [4]. A systematic review found tourniquet use reduced intra-operative blood loss (198 ml) and operating time (5 min), but did not affect post-operative blood loss or the possibility of requiring transfusion [4]. Tourniquet use increased the risk of thrombotic events such as deep vein thrombosis (DVT) and pulmonary embolism (PE) (risk ratio (RR) 5.00; 95% CI, 1.31 to 19.10), and non-thrombotic complications such as reoperation, haematoma, or nerve palsy (RR, 2.03; 95% CI, 1.12 to 3.67). Knee range of movement in the first 10 days post-operatively was 10.4 degrees less in the tourniquet group. More recently, Rathod et al. [7] found no difference in cement penetration when a tourniquet was used from incision to arthrotomy closure compared to using a tourniquet only during cementation. Pfitzner et al. [8] found cement mantle thickness was 1.2 mm (*p* = .009) greater in the tourniquet group than non-tourniquet group, and Ledin et al. [9] found no difference in prosthesis migration in tourniquet versus non-tourniquet TKR. Several investigators have reported higher post-operative pain when a tourniquet was used compared to no tourniquet [9–11].

Quadriceps function influences post-operative physical performance, functional ability and rehabilitation following TKR [12, 13]. Quadriceps dysfunction following TKR can be immediate, profound and persist for years after surgery, resulting in substantial functional deficits [14]. Mizner et al. [15] found quadriceps strength was 62% less than pre-operative values when measured four weeks after TKR.

Tourniquet use during TKR has been implicated in quadriceps dysfunction. Two studies, both with small samples (*n* = 20 & 28) assessed muscle function following TKR. Liu et al. [16] found that tourniquet patients had significantly less quadriceps muscle activity on EMG for the first six months post-operatively, as well as increased pain on day two and four post-operatively compared to non-tourniquet patients. Dennis et al. [17] found tourniquet patients had less isometric quadriceps strength when assessed with a force transducer at three weeks and three months post TKR compared to non-tourniquet patients.

The mechanism to explain quadriceps dysfunction following TKR and tourniquet use is unclear. A commonly accepted pathway is that ischaemia induces acute inflammation, degeneration and necrosis of muscle fibres [18]. Muscle biopsy following anterior cruciate ligament surgery with tourniquet found an accumulation of lysosomes, edema of fibres and endothelium, and fibre necrosis [18]. Tourniquet use might also injure nerves and/or delay nerve conduction and muscle activation. Mizner et al. [15] investigated quadriceps strength after TKR and found loss of strength was largely explained by a combination of reduced voluntary muscle activation and atrophy, but muscle activation played a greater role. Interestingly, most activation failure seemed unrelated to knee pain during muscle contraction, contrary to suggestions of pain-induced muscle inhibition.

### Objectives

The primary objective of this study is to determine whether non-tourniquet use during TKR reduces quadriceps strength less than tourniquet use when measured three months post-operatively.

A secondary objective is to determine whether non-tourniquet use during TKR reduces quadriceps strength less than tourniquet use at day 2 and 5, and 12 months post-operatively.

Other secondary objectives are to determine the effects of tourniquet use on:Pain and analgesia requirementsSelf-reported physical function and quality of lifeBlood loss and replacementSurgeon satisfaction with the intra-operative visual fieldOperation and anaesthetic timeComplications including revision surgeryCement mantle qualityPatient satisfactionHospital length of stay

## Methods

### Study design

The study is a single centre, parallel-arm, double-blinded (participant and assessor), randomised trial with 1:1 random allocation. The study schedule is summarized in Table 1.

**Table 1 Tab1:** Study schedule

	Pre-randomisation	Surgery Day 0	Post-surgery				
			Day 2	Day 5	During inpatient stay	3 months	12 months
Enrolment							
Eligibility screen	X						
Informed consent	X						
Randomisation		X					
Interventions							
Tourniquet TKR		X					
No tourniquet TKR		X					
Assessments							
Demographic variables	X						
Quadriceps strength	X		X	X		X	X
Blood loss and replacement		X			X		
Surgeon satisfaction		X					
Operation and anaesthetic time		X					
Tourniquet inflation time		X					
Pain			X	X			
Morphine equivalent daily dose					X		
Complications					X		
Knee Society Score	X					X	
Oxford Knee Score	X					X	X
WOMAC	X					X	X
EQ-5D-5 L	X					X	X
Revision surgery							X
Cement mantle							X

### Setting

The study will be conducted at a large regional public health service in Victoria, Australia. Twelve surgeons perform TKRs at the centre, all of whom will be involved in the study. In 2014, 149 primary TKRs were completed at the centre.

### Eligibility criteria

Eligible participants must have the following characteristics:Undergoing primary TKR for primary osteoarthritis≥ 18 years of ageWilling, able and mentally competent to provide informed consent (able to read and understand the Patient Information and Consent Form which is written in English language).

People who have the following pre-operative characteristics are not eligible:Undergoing bilateral TKR (as participant characteristics and rehabilitation are different to unilateral TKR)Neurological deficit affecting the surgical knee (due to potential effects on quadriceps strength)Rheumatoid arthritis (different aetiology than osteoarthritis)Pre-operative knee flexion < 60° (degree of flexion required for strength testing)Varus/valgus deformity > 15° (requires different surgical approach)Opioid tolerant (current use of oxycontin, opioid patches, or tramadol; > 4 tabs panadeine forte per day) (unable to assume standardised analgesia pathway)Sulphonamide allergy (to allow parecoxib/celecoxib use)Intolerant/allergic to oxycodone (unable to assume standardised analgesia pathway)Poorly controlled diabetes (HbA1C > 8) (impacts on choice of dexamethasone as antiemetic)Cognitively impaired (mini-mental state examination of < 25/30 [19]) (affects consent and participation in rehabilitation)eGFR < 60 mL/min/1.73m^2^ (allows parecoxib/celecoxib use)Privately insured patients (unable to follow-up)

All patients attending the study-site for pre-operative assessment for TKR will be assessed for eligibility by the surgeon, orthopaedic registrar or research coordinator. Eligible participants will be invited to participate in the study and informed written consent obtained as appropriate. Participation in the study is voluntary; no financial incentives will be offered.

Considering the expected number of participants fulfilling inclusion and exclusion criteria at the study site, recruitment is expected to occur over a 4-year period, commencing in October 2014.

### Randomisation

People who meet eligibility requirements and provide informed consent will be randomly allocated to either tourniquet or non-tourniquet groups with a 1:1 allocation ratio in blocks of 10. The allocation sequence will be computer generated by the research coordinator prior to trial commencement. Allocation will be concealed until immediately prior to anaesthetic induction, at which time the surgeon will access the allocation code for that participant via an opaque sealed envelope.

### Blinding

All participants, clinical staff and research staff will be blinded to group allocation, with the exception of the treating surgeon/s and theatre staff.

### Surgery

One of 12 surgeons will complete each TKR, with training registrars operating under direct supervision. Prosthesis type and whether to use navigated or non-navigated TKR is at the surgeon’s discretion, which will be decided upon prior to knowledge of the participant’s group allocation. A medial parapatella approach and no drain will be used for all participants.

The tourniquet group will have a tourniquet applied with padding. After exsanguination of the operated limb using a rubber tube or esmarch exsanguinator, the tourniquet will be inflated to 100 mmHg above systolic blood pressure or 250 mmHg, whichever is higher. The tourniquet will be deflated immediately prior to wound closure.

All participants receive intravenous Tranexamic Acid (TXA) to reduce peri-operative bleeding. The typical dose is 1 g TXA diluted in 100 ml normal saline infused intravenously at induction. Once the participant is in the recovery room, a second dose of 1 g TXA in 100 ml normal saline is given via infusion pump over 8 h (12.5 ml/hr).

All participants receive DVT prophylaxis commencing six hours after TKR unless contraindicated: clexane 40 mg daily for 14 days. Mechanical DVT prophylaxis via foot pumps will be applied until the patient commences ambulating at least 5 m daily.

### Anaesthesia, pain management and transfusion

Anaesthesia and analgesia are according to the organisation’s standardized protocols. All participants receive general anaesthesia with inhaled sevoflurane. Post-operative analgesia includes sub-sartorius saphenous nerve catheter infusion with patient controlled boluses, and paracetamol, celecoxib and oxycontin. Oxycodone is given for breakthrough pain. If a participant reports severe posterior knee pain that is unresponsive to first-line analgesia, a single sciatic nerve block will be considered.

Blood transfusion will occur if 1) the participant’s haemoglobin is less than 80, or less than 100 for patients with a history of significant cardiac pathology such as ischaemic heart disease or 2) the participant is hypotensive (i.e. systolic blood pressure < 100 mmHg and associated tachycardia) with suspected hypovolemia that is unresponsive to crystalloid/colloid fluid replacement.

### Post-operative care and rehabilitation

Post-operative care of all participants, irrespective of group allocation will be according to the organisation’s TKR protocols and care pathways. Participants are mobilized day-one post-operatively and participate in a daily rehabilitation program as coordinated by Allied Health staff. Participants are discharged to their usual place of residence once they are medically fit and sufficiently independent with activities of daily living. Participants are sent to inpatient rehabilitation if they are not sufficiently independent to manage at home, which often coincides with living alone. Following discharge from inpatient care, all participants receive ongoing rehabilitation under the direction of Allied Health staff, which is ceased at the discretion of staff and participants. The organisation’s care pathways allow professional discretion regarding the amount and content of rehabilitation completed. Complete standardization of each group’s rehabilitation program is beyond the jurisdiction of the current study and is a potential limitation. Participation in ongoing rehabilitation will be recorded, equivalence between groups assessed and differences will inform data analysis and interpretation.

### Outcome measures and assessment time points

The primary outcome is the maximum percentage change in isometric quadriceps strength assessed preoperatively and 3 months following TKR. Strength will be measured in Newtons and assessed using a fixed-base electromechanical dynamometer (IsoForceControl EVO2 dynamometer [20]) with the knee stabilised in 60 degrees of flexion. Patient will be seated in a customised chair with a frame that fixes the dynamometer in position. The force plate will be applied adjacent to the malleoli of the ankle. Following 1–2 practices, participants will extend their knee as forcefully as they can for 10 s. The maximum force from three consecutive attempts will be recorded. Fixed-based dynamometer has very good to excellent reliability in people following arthroplasty [21].

Quadriceps strength at day 2 and 5, and 12 months post-operatively are secondary outcomes. Other secondary outcomes include:Post-operative inpatient pain and analgesia requirementsKnee pain intensity on day 2 and 5 post-operatively according to a 0–10 numeric scale (0 = no pain, 10 = extreme pain)Morphine equivalent daily dose [22] (mg, average for first 5 days)Blood loss and replacementIntra-operative blood loss (ml, sucker bottle minus irrigation volume)Transfusion (units)Surgeon satisfaction with intra-operative visual field1–10 numeric scale (1 = completely unsatisfied, 10 = completely satisfied)Operation and anaesthetic time (minutes)Complications during inpatient stayDVT or PEWound complications such as infection, haematoma or breakdown which require a change in management such as antibiotics or reoperationMedical complications (Medical Emergency Team (MET) calls [23] or death)Hospital length of stay (days)Self-reported pain, physical function and quality of life at 3 and 12 monthsKnee Society Score (KSS) [24]Oxford Knee Score (OKS) [25]WOMAC [26]EQ-5D-5 L [27]Revision surgery within 12 monthsCement mantle quality at 12 months [28]Patient satisfaction at 3 and 12 months

Strength measurements will be collected by research assistants, who are trained by a study investigator. The KSS will be completed by the treating surgeon, training registrar or resident. Participants will complete standardised questionnaires in paper-format with assistance offered by a research assistant as required. Cement mantle quality will be determined by a surgeon or research assistant trained by a surgeon. Data for the remaining outcomes will be extracted from the participant’s medical record. Research assistants will enter data into REDCap, the study’s password-protected electronic data collection and management tool hosted by the institution [29].

The study will collect baseline demographic information including age, sex, height, body weight, American Society of Anesthesiologists (ASA) score [30], cognitive function (mini-mental state examination [19]) and medical comorbidities summarized with the Charlson Comorbidity Index [31]. Prosthesis type and the use of navigated or non-navigated procedures will be recorded.

Once participants are enrolled in the study and undergone surgery, every reasonable effort will be made to reassess them for the entire study period. Research assistants will attempt to contact participants a maximum of four times over a three-month period using phone, email or mail before they are considered lost to follow-up. Participants may withdraw from the study at any time and for any reason. Participants will be invited, though not required, to indicate reasons for withdrawal. Those wishing to withdraw from the study will be invited to complete questionnaire assessments via mail rather than attending reassessment/s in person.

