### Statistical analysis plan

The main results will be based on intention-to-treat analysis which will include all participants as randomised. Per protocol analysis will also be conducted as secondary analysis and include only patients whose surgery was completed as randomised. All categorical data will be summarised using frequencies and percentages and baseline characteristics will be compared using the Chi-squared statistic. Interval or continuous data will be summarised using means with standard deviations or medians with lower and upper quartiles if the data are skewed. The amount of missing data for each group and each outcome will be described with frequencies and proportions. Analysis will include cases with available data. No imputation of missing data will occur. For questionnaire data, if a participant has not responded to ≥15% of questions in a questionnaire (or subscale where relevant), the responses for that scale will not be included in the analysis.

Linear mixed models [33] will be used for group comparisons of quadriceps strength at the different follow-up time points (2 days, 5 days, 3 months and 12 months). The major advantages of using this method are that it accounts for intra-individual correlations in observations, multiple variables can be included in the model and the method uses all available data even in the presence of unbalanced data. If assumptions permit, the restricted maximum likelihood approach will be adopted. The models will include an interaction term between time and treatment group, which will indicate the between group differences in quadriceps strength changes from baseline. The linear mixed model will also be considered for the analysis of continuous secondary outcomes that are available at multiple follow-up time points (> 3 time points). Other continuous outcomes that are only assessed at baseline and once/twice at follow-up will be analysed using linear regression, allowing for estimation of clustered sandwich error estimates [34]. Non-parametric models such as quantile regression will be considered for cases where assumptions of linear models are not satisfied.

Secondary outcomes that are categorical will be analysed using logistic regression models [35]. Count data such as hospital length of stay will be analysed using Poisson regression or other count-data models (e.g. negative binomial regression) if the assumptions of the Poisson regression models are not satisfied [36].

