### Sample size

The sample size was calculated on the basis of the primary outcome. To the best of the our knowledge, at the time of study development there was no published data reporting quadriceps strength following tourniquet use and total knee replacement that could be used to estimate a sample size for this study. Therefore, allowing for a medium to large effect size (Cohen’s d = 0.65), based on the large quadriceps function differences between groups observed by Liu et al. [16] which were measured using surface electromyography, a two-sided significance level of α = .05 and power of 80%, a minimum sample size of 39 participants per arm was estimated. Allowing for a 15% drop-out rate, we aimed to recruit 45 participants to each group.

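### The primary outcome is a percentage change in quadriceps strength, but the only strength model described does not name percentage change as its response or say how baseline enters, so outcome and analysis need reconciling

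*Protocol article*

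**What the plan says.** Under Outcome measures and assessment time points, the protocol article declares: "The primary outcome is the maximum percentage change in isometric quadriceps strength assessed preoperatively and 3 months following TKR". The next sentence gives the unit: "Strength will be measured in Newtons".

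The Statistical analysis plan section gives one group comparison for strength: "Linear mixed models [33] will be used for group comparisons of quadriceps strength". The follow-up times listed for it are "2 days, 5 days, 3 months and 12 months". The model has a time-by-group interaction, "which will indicate the between group differences in quadriceps strength changes from baseline". No covariate is named, although the section lists among the method's advantages that "multiple variables can be included in the model".

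The Sample size section says "The sample size was calculated on the basis of the primary outcome". It uses Cohen's d = 0.65, two-sided alpha 0.05 and 80% power, giving 39 per arm. The effect size is borrowed from surface electromyography differences in a small earlier study. The section does not say whether d is in units of the standard deviation (SD) of percentage change, of change in Newtons or of strength at follow-up.

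**The concern.** A time-by-group interaction in a linear model of a quantity measured in Newtons is a difference in absolute change. The declared outcome is a proportional change. These are different quantities: a 20% loss is 30 N for a patient who starts at 150 N and 80 N for one who starts at 400 N, so the two scales weight patients differently and can give different p-values.

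The time points add a second uncertainty. If only the four follow-up visits are in the model and day 2 is the reference, the interaction compares changes since day 2, not since baseline. If percentage change is the response, it is already a change from baseline, and the interaction is again not the 3-month group difference by itself. On neither reading does the stated interpretation follow from the model as listed.

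At stake is the trial's single primary result. Two defensible headline analyses leave room for choice after the data are seen, and the 80% power cannot be attached to both.

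**Working it through.** **1. The plan's own figure.** Inputs from the Sample size section: d = 0.65, two-sided alpha 0.05, power 80%. A two-sample t-test needs 38.14 per arm, rounded up to 39. Power at 39 per arm is 0.809 (t-test). By the normal approximation, 0.65 × √(39/2) = 2.870; 2.870 − 1.960 = 0.910; Φ(0.910) = 0.819. The 39 reproduces for a plain two-group comparison of whatever quantity d refers to, with no gain from baseline adjustment assumed.

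**2. What baseline adjustment gains.** Let r be the correlation between baseline and 3-month strength, with equal SDs at both times. The documents do not give r, so a range is used. Relative to the SD at follow-up:
- the SD of change is √(2(1 − r));
- the SD after baseline adjustment is √(1 − r²);
- the variance ratio, adjusted to change, is (1 − r²)/(2(1 − r)) = (1 + r)/2.

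If d = 0.65 is on the SD of change, the change comparison has power 0.819 for every r. Adjustment raises the effective d to 0.65/√((1 + r)/2). For r = 0.7 that is 0.65/√0.85 = 0.705; 0.705 × √(39/2) − 1.960 = 1.153; Φ = 0.876.

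| r | Change, unadjusted | Baseline-adjusted | Gain (points) | n per arm for 80%, adjusted |
|---|---|---|---|---|
| 0.3 | 0.819 | 0.945 | 12.6 | 25 |
| 0.5 | 0.819 | 0.912 | 9.3 | 28 |
| 0.7 | 0.819 | 0.876 | 5.7 | 32 |
| 0.8 | 0.819 | 0.857 | 3.8 | 34 |
| 0.9 | 0.819 | 0.838 | 1.9 | 36 |

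**3. When power falls below 80%.** Extra assumptions are needed.
- With d on the SD at follow-up, the change comparison has power 0.679 at r = 0.3, 0.819 at r = 0.5 and 0.960 at r = 0.7. The adjusted analysis has 0.853, 0.912 and 0.980.
- With d on the SD of change and a comparison of follow-up values only, power is 0.819 at r = 0.5 and 0.604 at r = 0.7.

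**4. Does the scale matter?** This was simulated with 39 per arm and 4000 trials per scenario. All of the following are assumptions: log-normal strength, coefficient of variation 35 to 45%, r from 0.5 to 0.8, follow-up mean 0.85 of baseline without tourniquet, and a multiplicative tourniquet effect.

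| d = 0.65 set on | Change in Newtons | Log force adjusted for log baseline |
|---|---|---|
| Percentage change | about 60–66% | about 85–94% |
| Change in Newtons | about 80–83% | about 97–99% |

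With d set on percentage change, the percentage-change comparison itself had 80–83%, and Newtons adjusted for baseline about 80–91%. The choice of scale moves power noticeably, but the direction against 80% depends on which scale d belongs to, and the document does not say.

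**The case against.** The strongest reply is that this is ambiguity, not a proven mismatch. The analysis section never says the response is in Newtons; that unit comes from the description of the measurement. The word strength may be shorthand for the declared outcome. The omission of baseline from the listed visits even fits percentage change as the response at each follow-up, with baseline in the denominator. This stands as far as it goes: a reader might infer that the plan has committed to absolute change, and the text does not establish that. But the alternative reading is not stated either, and it sits awkwardly with an interaction described as giving change from baseline.

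A reader might also infer that baseline is ignored. The documents do not support that. The interaction is meant to capture change from baseline, covariates are allowed, and a covariate list may be left to a fuller plan that is not shown. A mixed model with baseline among the responses and a common baseline mean would be close to a baseline-adjusted analysis.

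A third tempting inference is that the trial is underpowered at around 60%. Section 4 of the working shows that this rests on placing d on percentage change; placed on change in Newtons, the shortfall disappears.

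Nor do the documents show that weak, painful knees will produce extreme percentages or that quantile regression is likely. The plan says only that non-parametric models will be considered if assumptions fail.

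What survives is that a declared primary outcome and a described model, both fixed in the same article, are not linked.

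**Conclusion.** The point holds as a failure to tie the primary outcome to its analysis. Percentage change is declared but never named as a response; baseline is missing from the model's visits although the interaction is read as change from baseline; and d = 0.65 has no scale. On the natural reading the model estimates an absolute change, but the text does not settle it.

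The size is best stated as precision forgone. Against an unadjusted change comparison, baseline adjustment is worth about 2 points of power at r = 0.9 and about 13 at r = 0.3, if d is on the SD of change; r is assumed. It is not an established loss against the stated 80%. The figure of roughly 60 to 66% for change in Newtons needs both a multiplicative effect and d on percentage change, together with the assumed distribution. The matter should be settled before unblinding because it concerns the one result on which the trial will be judged.

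**What to change.** Before unblinding, state in one place:
- the response variable of the primary model;
- the 3-month group contrast as the primary test;
- how baseline strength enters, either as a covariate or as a response with a common baseline mean;
- the scale to which d = 0.65 refers.

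A suitable choice is log maximum force in the mixed model, adjusted for log baseline force, with the 3-month group difference back-transformed to a ratio. This keeps the proportional meaning of the declared outcome. Raw percentage change can be reported descriptively. If the team prefers Newtons, a baseline-adjusted model in Newtons also works, with the primary outcome reworded to match.

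No new data are needed, since baseline strength is already scheduled for every participant. There are two small costs to the log scale: the effect is reported as a ratio of geometric means, and a zero force at day 2 or 5 has no logarithm, so a handling rule must be written in advance. Recruitment was planned over four years from October 2014, so any rewording of the primary outcome should be a dated, documented amendment that records that allocation was still concealed from the analysts.
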